## 3. Method

The Local Ethics Committees approved the project protocol (ASL_BO n. 0115481 provided on 18/10/2022) before commencing the recruitment and registered to ClinicalTrials.com (ID: NCT06164054) The study is performed according to the principle of the Helsinki Declaration. The study results will be disseminated in peer-reviewed scientific journals and in abstract format at scientific events.

### 3.1. Study design

A single-blind (the patient is blind to group assignment) two-arm randomized controlled trial is proposed with a blocking randomization [39]. Participants who have had a stroke are randomly allocated to: (1) 4 weeks traditional rehabilitation program (control group), or (2) 4 weeks to Virtual Reality rehabilitation program (experimental group). The study design presents 4 measurement times: pre-intervention, immediately after the intervention, and two follow-ups (at 6 and 12 months; see Fig 1). The rehabilitation programs, both experimental and control, will be performed at the Bellaria Hospital of Bologna (Italy). Moreover, participants must sign written consent forms for study participation and personal data handling and management.

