#### 3.4.1. Virtual Reality rehabilitation setting

The VR protocol uses two types of technology: three-dimensional (3D) and two-dimensional (2D). During the 3D session, patient sits on a chair and wear the head-mounted display (HMD) while performing some exercises. The exergames consist of tasks requiring precision movements, such as building some blocks, putting the virtual block in a specific position, moving the virtual object inside the environment, paint and colouring some proper figures (Fig 2a). The 2D session is performed by the Virtual Reality Rehabilitation System-Handbox (Khymeia Group, Noventa Padovana, Italy) technology for hand and wrist rehabilitation that tracks the patient’s hand and project it to a monitor without the need to wear any sensor or HMD. Patient sits on a chair, and the monitor screen is positioned at a 1.5 m distance in front of the patient (Fig 2b). Through the Handbox, the patient executes hand exergames based on the pinch, grasp, single finger coordination, wrist movements, customized according to the patient’s motor ability. For both technologies, 3D and 2D, the arm and fingers are captured and projected onto the screen through the Leap Motion Controller. This advanced motion sensor device uses infrared cameras and LEDs to detect and track the position, orientation, and movement of each finger and the hand as a whole. It captures movements at a high frame rate, ensuring smooth and responsive interaction, reproducing an effect similar to the traditional mirror box [58]. For the 3D condition, the Leap Motion Controller is incorporated into the HMD, while for the 2D condition, it is integrated into the Handbox. Both systems allow patients to interact with virtual objects in a natural and intuitive manner. For example, patients can reach out, grab, move, and manipulate virtual objects as they would in the real world. During both sessions, 3D and 2D, there is the constant supervision of the physiotherapist and researcher supervision that guide the patients, directing their focus on the exercises and providing encouragement throughout the tasks.

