#### 3.4.3. Control treatment

Participants randomly assigned to the control group will receive rehabilitation treatment as per usual clinical practice. Specifically, patients will be directed to rehabilitation facilities according to standard clinical rehabilitation pathways. They will be assigned to a physiotherapist who will administer the rehabilitation treatment for the upper limb impairment. Patients in the control group will receive the same amount of rehabilitation for the recovery of upper limb impairment as the treatment group, which means 3 physiotherapy sessions lasting 1 hour 3 times a week for 4 weeks. Based on the treatment intensity, a physiotherapist ensured that the control group received the same level of treatment as the experimental group in terms of the physical effort required by patients.

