#### 3.5.1. Primary outcome

The primary outcome measures will be the Fugl-Meyer for Upper Limbs [45] employed as a performance-based assessment to characterize motor recovery in research, has demonstrated outstanding reliability. This encompasses internal consistency, inter-rater reliability, intra-rater reliability, and test-retest reliability, particularly in the post-stroke context [59]. The assessment includes 33 items to evaluate upper extremity motor impairment and is scored between 0 and 2 (0 = unable, 1 = partly able, and 2 = fully able to complete movement) with a total score range of 0–66. The assessment will be performed before treatment (T1), after the conclusion of the treatment (T2), and after 6 months as a follow-up (T3).

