#### 3.5.4. Recruitment and randomization

Patients considered eligible according to the inclusion criteria will be invited from the IRCCS Istituto delle Scienze Neurologiche di Bologna to participate in the study, explaining in detail the purposes and methods of the study. Before enrolment, informed consent will be obtained from patients. Then, to minimize the risk of bias, the Random Allocation Software 2.0 will be adopted to randomize participants and organize them into blocks of six, that is three participants receiving traditional rehabilitation and three participants receiving the Virtual Reality rehabilitation.

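### The trial is labelled single-blind on the ground that patients are blinded, which headset VR against ordinary physiotherapy does not allow, and no blinding is claimed for the rater of the Fugl-Meyer primary outcome

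*Protocol article*

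**What the plan says.** The protocol article makes one statement about blinding. Section 3.1 describes "A single-blind (the patient is blind to group assignment) two-arm randomized controlled trial".

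The other relevant statements are these:

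- **Information before consent (Section 3.5.4):** eligible patients are invited, "explaining in detail the purposes and methods of the study".
- **Experimental arm (Section 3.4.1):** in the 3D session the "patient sits on a chair and wear the head-mounted display (HMD) while performing some exercises". The 2D session uses the Handbox and a monitor. Section 3.4.2 gives every experimental patient both.
- **Control arm (Section 3.4.3):** "Participants randomly assigned to the control group will receive rehabilitation treatment as per usual clinical practice". No sham headset or sham VR task is described.
- **Staff at VR sessions (Section 3.4.1):** "there is the constant supervision of the physiotherapist and researcher".
- **Primary outcome (Section 3.5.1):** the upper-limb Fugl-Meyer, "employed as a performance-based assessment to characterize motor recovery in research", has 33 items, each "scored between 0 and 2 (0 = unable, 1 = partly able, and 2 = fully able to complete movement", with a total of 0 to 66.
- **Secondary outcomes (Section 3.5.2):** Box and Blocks, MAIA, the Rubber Hand questionnaire, FIM and SSEQ, with treatment satisfaction (CSQ-8, Table 1) at T2.
- **Allocation (Section 3.5.4):** software is used to randomise patients and "organize them into blocks of six", three per arm.

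**The concern.** The label states a property that the rest of the article rules out. The two treatments look and feel different, nothing masks the difference, and patients are told how the study works before they agree to it.

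The label is also defined in a way that leaves the rater out. Section 3.1 does not just use the term single-blind; it says in parentheses which party is meant, and that party is the patient. The primary outcome depends on someone judging whether a movement is absent, partial or complete, and nothing in the article claims that this person is kept unaware of the arm.

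Three things are at stake:

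- A report that repeats the label would mislead readers about the trial's risk of bias.
- The primary outcome has no declared protection against a rater's expectations.
- Hypotheses 2 and 3 lean on self-reports (MAIA and the Rubber Hand questionnaire for proprioception, CSQ-8 for satisfaction), which patients complete knowing their treatment. Hypothesis 3 also expects more abandonment under usual care, and Section 3.7 removes dropouts from the analysis. If knowledge of the arm affected who left, it would also affect who is analysed.

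**Working it through.** The main check sets the sections side by side.

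**1. Can the patient be blind to the arm?**

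- Before consent the patient learns the aims and methods (Section 3.5.4), and so can be expected to know that VR is compared with traditional rehabilitation.
- At the first session the patient either does virtual tasks with a headset and the Handbox (Sections 3.4.1 and 3.4.2) or has usual physiotherapy (Section 3.4.3).
- No sham is described that would make the arms look alike.

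The patient therefore knows the arm. At most, a patient could be unaware of the hypotheses, but Section 3.1 says something else: that the assignment itself is hidden.

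**2. Is blinding claimed for anyone else?**

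No. Section 3.1 names only the patient. The staff who attend VR sessions (Section 3.4.1) necessarily know the arm. Sections 3.3.1, 3.5.1 and 3.5.2 do not say who rates the Fugl-Meyer or Box and Blocks, or what that person knows.

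**3. Which outcomes are affected?**

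- Rated by an observer: Fugl-Meyer (graded movements) and Box and Blocks (a count in 60 seconds).
- Self-reported: MAIA, Rubber Hand questionnaire, SSEQ and CSQ-8. These cannot be blinded in this design.

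**4. Scale of the primary outcome (an illustration, not an estimate)**

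The maximum is 33 × 2 = 66. If every patient in one arm, and none in the other, were graded one step higher on k items, the mean difference would move by k points. The documents give no value for k. As an assumed range:

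- k = 1: 1 point, 1/66 = 1.5% of the scale
- k = 3: 3 points, 3/66 = 4.5% of the scale

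**5. Blocks of six (supporting and conditional)**

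Suppose an enroller knows the block size, where each block starts and every earlier allocation. With m = 3 per arm there are C(6,3) = 20 possible sequences.

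- Allocations fixed by earlier ones: 2m/(m+1) = 6/4 = 1.5 of 6 = 25%
- Correct guesses, naming the arm with more places left and tossing a coin when equal: m + 2^(2m−1)/C(2m,m) − 1/2 = 3 + 32/20 − 0.5 = 4.1 of 6 = 68.3%

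Listing all 20 sequences gives the same results. With 60 patients (30 per group, Section 3.5.3) there are 60/6 = 10 blocks, so 15 allocations would be certain and 41 guessed correctly. Simple randomisation gives 50%.

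For other known block sizes:

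| Block size | Certain | Guessed correctly |
|---|---|---|
| 4 | 33.3% | 70.8% |
| 6 | 25% | 68.3% |
| 8 | 20% | 66.6% |

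A different known size changes little. Any gain from varying sizes comes from the enroller not knowing where a block ends, and that gain is not quantified here.

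**The case against.** The strongest case on the other side is that this is a condensed article. Who rates the outcomes, what raters know and how allocation is concealed are commonly left to the full protocol, so silence on these is no error. That stands, and the absence of a concealment procedure is not counted here. It does not rescue the label, because Section 3.1 makes a positive statement and defines it, and nothing else in the article makes that statement true.

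Three stronger readings are tempting, and the document does not support them.

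- **That raters are unblinded, or that the researcher who supervises VR sessions also rates.** A reader might infer this because nothing excludes it. The article never says who rates. The supportable statement is that no rater blinding is claimed.
- **That blocks of six make allocation predictable.** A reader might infer this from one published block size and openly visible treatment. The figures in the working need an enroller with three pieces of information, and the article does not show that anyone has them. Section 3.2 has patients informed by referring doctors at check-up visits, and these are not said to be the staff who supervise sessions. That the block size is constant is itself inferred from a single stated size.
- **That the primary result is biased by some number of points.** The item-grade arithmetic describes the scale. It has no source in the documents as a measure of leniency.

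It is also fair to say that satisfaction with an openly different treatment can never be blinded. For the self-reports, the answer is accurate labelling and cautious interpretation, not a redesign.

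**Conclusion.** The point holds in this form. The article declares patients blind, and its own description of the arms and of recruitment makes that impossible. Since the declaration covers patients only, the observer-graded primary outcome and the Box and Blocks test have no claimed blinding. Both should be put right before results are reported.

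The size of any bias cannot be derived from the document. The conclusion does not need a size: it rests on the visible difference between the arms, the absence of any described sham and the explanation given before consent.

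The block-size point is secondary. The 25% certain and about 68% guessable are correct only under the stated knowledge conditions, which the document does not establish, so it supports an optional improvement and no more.

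**What to change.** **Label.** Replace the wording in Section 3.1 with: *patients and therapists unblinded; outcome assessor blinded*.

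**Rater.** Have the Fugl-Meyer and Box and Blocks rated at every assessment by an existing member of the multi-professional team described in Section 4 who does not treat or supervise that patient and is not told the arm. If this is not feasible, call the trial open-label.

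**Self-reports.** Report MAIA, the Rubber Hand questionnaire, SSEQ and CSQ-8 as unblinded, and interpret Hypotheses 2 and 3 with that in mind.

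**Optional.** Use varying, undisclosed block sizes for future allocations, leaving past ones intact.

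**Cost.** Some rota planning and a less favourable blinding label. Sample size and interventions do not change. That a suitable rater is available is an assumption: Section 4 lists professions, not staffing. The value of a new allocation list depends on how many patients remain to be enrolled, which the article does not state.

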**Fig 1 pone.0307408.g001:**
[figure not shown]
CONSORT flowchart.

### 3.2. Participants

The participants’ groups involve people with stroke selected according to inclusion and exclusion criteria and keen to participate in the study. Patients are enrolled in the Neurorehabilitation Unit of the Institute for Neurological Sciences of Bologna (Istituto delle Scienze Neurologiche di Bologna, ISBN). Furthermore, the potential participants are informed about participation in the study during the check-up visits scheduled by ISNB medical doctors referring the patients.

#### 3.2.1. Inclusion criteria

Patients must have all the following inclusion criteria: (a) Being 18 to 85 years old, both males and females; (b) Suffering from ischemic or haemorrhagic stroke; (c) The stroke event must have occurred from two to eighteen months before recruitment [40]; (d) Patients must have moderate to severe upper limb motor deficit established by a score of ≤ 80 on the Motricity Index [41], and the alteration of sensorimotor and proprioception abilities of the injury upper limb, established by the failure in 3 proofs up to 4 of the Thumb Location Test [19]; (e) Patients must understand and sign the written consent for enrolment.

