### 3.3. Assessment

The basic information, including age, sex, lesion side of the brain, stroke type, and duration after stroke onset, was recorded. The clinical outcomes include motor assessment, which examines the motor function of the patients’ injured upper limb, as well as neuropsychological assessment to evaluate cognitive abilities for the eligibility criteria and to investigate if the rehabilitation program could also impact the patient’s cognition. Additionally, patient’s self-efficacy and satisfaction toward the treatment are also evaluate.

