#### 3.5.3. Sample size

A sample size of 30 participants per group has been determined using G*Power 3.1.3. This calculation was based on a repeated measures ANOVAs (within and between subjects), considering a small to medium effect size of 0.2 [60], as also reported in a two-arm Randomized Control Trial involving chronic stroke participants that also adopted as primary outcome measure the Fugl-Meyer scale [61]. The sample size determination also accounted for 20% attrition, with a significance level (α) set at 0.05 and a desired statistical power of 0.80, as outlined in the literature [62]. Additional, participants will be enlisted in the event of any dropouts.

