### 3.7. Statistical analysis

The data analysis follows the Per Protocol approach, that is only participants who have adhered to the study protocol, patients who dropped out of the study are excluded from the analysis. Analysis will be performed through the Statistical Package for Social Sciences (SPSS). Descriptive statistics for both the experimental and control groups will encompass measures such as the mean and standard deviation. The student t-test for independent samples will be used to evaluate the baseline. In case of excessive deviation from normality, a similar non-parametric test (Mann-Whitney) will be used. Changes in motor performance and proprioception between T1 and the subsequent longitudinal evaluations (T2, T3) will be assessed using the repeated measures Analysis of Variance (rmANOVA) with a mixed design 2×3, considering the group as "between subjects" factor and the time point measure as "within subjects" factor. Residual plots will be inspected to verify linearity, normality and homoscedasticity assumptions for all models as well as to identify potential influential outliers. According to the literature, for all inferential analyses the probability of type 1 error is a-priori fixed at alpha α = 0.05 and will include reporting the 95% Confidence Interval for each estimate [62].

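### Time since stroke (2 to 18 months) is recorded but used in neither the stated allocation nor the stated Fugl-Meyer model, a precision gain forgone at almost no cost

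*Protocol article*

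**What the plan says.** All references are to the protocol article.

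- **Entry (3.2.1):** "The stroke event must have occurred from two to eighteen months before recruitment".
- **Baseline data (3.3):** "The basic information, including age, sex, lesion side of the brain, stroke type, and duration after stroke onset, was recorded".
- **Design (3.1):** a "two-arm randomized controlled trial is proposed with a blocking randomization".
- **Allocation (3.5.4):** the software will "organize them into blocks of six, that is three participants receiving traditional rehabilitation and three participants receiving the Virtual Reality rehabilitation". No stratification factor is named.
- **Model (3.7):** a "repeated measures Analysis of Variance (rmANOVA) with a mixed design 2×3". Its only two factors are group, between patients, and time point, within patients. No covariate is named.
- **Baseline comparison (3.7):** "The student t-test for independent samples will be used to evaluate the baseline", with Mann-Whitney as the non-parametric alternative.
- **Size (3.5.3):** 30 per group, allowing for 20% attrition.

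**The concern.** The window is wide: 18 months is nine times 2 months. It is plausible, though no section says so, that patients treated soon after a stroke change more on the Fugl-Meyer scale over the study than patients treated late, whichever arm they are in.

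The within-subject factor removes differences between patients in their starting level. It does not remove differences in how much they change, and those go into the error term against which the group-by-time effect is tested. With 30 per arm or fewer, any variance that a recorded baseline value could explain is worth recovering. What is at stake is power and the width of the confidence interval for the group difference in change.

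**Working it through.** **Plan's own figure.** The plan gives no figure on this point. The only figure used from it is 30 per group, or 30 × 0.8 = 24 per group after the stated attrition. That size can be neither confirmed nor refuted, because section 3.5.3 gives neither the correlation between time points nor the effect tested. With three time points and effect size f = 0.2, the interaction test needs 42 in total at correlation 0.5 (42/0.8 = 52.5, so 53). It needs 46–48 at correlation 0.43–0.47, which inflates to 58–60. The point does not depend on this.

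**Assumed inputs (not in the documents).**
- Share of early patients, p: 0.25 or 0.50.
- Extra Fugl-Meyer gain in early patients irrespective of arm, g: 3, 5 or 8 points.
- SD of change within early or late patients, s: 5 or 8 points.

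**Step 1, variance explained.** A two-group mixture adds v = p(1 − p)g² to the variance of change, so R² = v/(v + s²).
- Lowest: p = 0.25, g = 3, s = 8 gives v = 1.69 and R² = 1.69/65.69 = 0.026.
- Highest: p = 0.50, g = 8, s = 5 gives v = 16 and R² = 16/41 = 0.390.

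**Step 2, power forgone.** Take a two-arm comparison of change with n = 24 per arm and a true difference that gives 80% power at residual SD s. The standardised difference is (1.960 + 0.842) × √(2/24) = 0.809. Without adjustment the SD is √(v + s²), so power = Φ(2.802 × √(1 − R²) − 1.960).
- Lowest R²: Φ(2.802 × 0.987 − 1.960) = Φ(0.805) = 0.79.
- Highest R²: Φ(2.802 × 0.781 − 1.960) = Φ(0.228) = 0.59.

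| p | g | R², s = 5 | Power unadjusted, s = 5 | R², s = 8 | Power unadjusted, s = 8 |
|---|---|---|---|---|---|
| 0.25 | 3 | 6.3% | 77.4% | 2.6% | 79.0% |
| 0.25 | 5 | 15.8% | 72.9% | 6.8% | 77.2% |
| 0.25 | 8 | 32.4% | 63.4% | 15.8% | 72.9% |
| 0.50 | 3 | 8.3% | 76.5% | 3.4% | 78.6% |
| 0.50 | 5 | 20.0% | 70.7% | 8.9% | 76.2% |
| 0.50 | 8 | 39.0% | 59.0% | 20.0% | 70.7% |

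This treats change as one contrast, whereas the planned test spans three time points. It shows the order of the loss, not the exact power of the 2×3 test.

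**Step 3, which term is needed.** Write time since stroke as X. If X enters only as a main effect βX, it is the same at every time point and cancels in the change T2 − T1: βX − βX = 0. The group-by-time test is then unchanged. With a covariate-by-time interaction, (β₂ − β₁)X remains and absorbs the differing change.

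**Step 4, cost.** Within-subject error degrees of freedom are (N − 2)(3 − 1): 116 at N = 60 and 92 at N = 48. The interaction uses 3 − 1 = 2, leaving 114 or 90.

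**The case against.** **The article may only be condensed.** Stratification factors and covariates could be named in a full protocol or analysis plan that is not shown. That is possible. But sections 3.5.4 and 3.7 go beyond silence: they give the block size and composition, the dimensions of the model and both of its factors, and time since stroke is in none of them. The baseline test in section 3.7 may well cover time since stroke, but a test adjusts for nothing.

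**The analysis as stated is valid.** This stands. A reader might infer that a chance excess of early patients in one arm would be mistaken for a treatment effect, or would overturn the conclusion on equal effectiveness. The documents do not support that. Random allocation prevents systematic imbalance, and chance imbalance is already counted in the unadjusted standard error, so the error rate and interval coverage hold. For scale, take 40% early patients, g = 3–8, s = 5–7 and 30 per arm. The standard error of the group difference is then about 1.3–2.1 points. A 20-percentage-point imbalance moves the difference by 0.20 × g = 0.6–1.6 points, or about 0.3–1.0 standard errors, and one that large or larger arises about 15% of the time. This is the same variance as in the working, not a second harm. Excluding dropouts under the per-protocol approach can disturb balance, but that is a separate matter.

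**Two other passages might seem to strengthen the point, and do not.** Section 5 mentions patients early in recovery, but in connection with complications and discontinuation, not Fugl-Meyer trajectories. Section 3.5.3 mentions a chronic-stroke trial, but only "as also reported in a two-arm Randomized Control Trial involving chronic stroke participants", so that trial is not shown to be the source of the effect size. The spread of change within it is not given either.

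**Every magnitude is assumed.** This also stands. If the gap in gain is small, the benefit is about one percentage point of power.

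**Conclusion.** The point holds as a missed gain in precision, not as an error that invalidates the trial. The documents establish four facts: the 2–18 month window, the recording of time since stroke, allocation in blocks with no stratum, and a model with group and time point only. The consequence is conditional: if change in Fugl-Meyer depends on time since stroke, the stated model leaves that variation in the group-by-time error term. Over the assumed ranges the loss runs from about 1 to 21 percentage points of power, against 80% with adjustment at 24 per arm. The documents cannot place the trial within that range. The change is worth making because the variable is already collected and the cost is close to nil.

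**What to change.** **In section 3.7**, prespecify time since stroke at enrolment, as log months, as a covariate together with its interaction with time point in the Fugl-Meyer and Box and Blocks models. Alternatively, model the T2 and T3 scores adjusted for the T1 score, with log months since stroke as a further covariate; this serves the same end. State this before the outcome data are examined, so that the choice cannot follow an observed imbalance. Keeping the covariate continuous avoids having to choose a cut.

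**Optionally, in section 3.5.4**, for patients not yet randomised, run the existing blocks of six separately in two strata of time since stroke, with the cut stated in advance.

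**Cost:** two within-subject degrees of freedom out of 92–116 and, if stratification is adopted, a second allocation list. No new patients, visits or measurements are needed.
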